### Statistical analysis

#### Sample size calculation

The study consists of two study groups: one group with suboptimal FHR patterns and one group with abnormal FHR patterns. We aim for the study to have 80% power and a level of significance of 0.05 in both groups. In one small, non-randomised study, a reduction in FHR decelerations (type II dips) of 50–100% was noted. Our present study is the only one to report FHR changes as a result of maternal hyperoxygenation. On the basis of available literature, we expect ≥ 50% improvement in the oxygen group and 0% in the control group in both suboptimal and abnormal FHR patterns [28]. We estimated a mean improvement of 50% with an SD of 50% in each group. A power analysis performed in G*Power 3.0.10 (Kiel University, Kiel, Germany) for a two-tailed Mann-Whitney *U* test (assuming that data will not be equally distributed) resulted in a sample size of 67 patients in each study group. We added an extra 20% to compensate for missing data. Because we have two separate study groups (suboptimal and abnormal FHR group), we need 162 patients to participate.

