In this study, we focus on the foetal condition during the second stage of labour and short-term neonatal outcome. This implies that abnormalities in FHR patterns during the first stage of labour are not taken into account. We believe that the randomisation process will limit its influence. With regard to the neonatal period, we did not arrange long-term follow-up, because we do not expect any clinically relevant side effects that can be attributed to maternal hyperoxygenation. Besides, the sample size is too small to draw firm conclusions on long-term neonatal effects in this study.

Power analysis of the present study is based on the expected effect on the primary outcome measure, and the study is not powered to find any significant differences in Apgar score and umbilical cord blood gas values. In the power analysis, we used an expected improvement in deceleration depth and duration of 50%. On one hand, this value is based on small non-randomised studies and may be overestimated. On the other hand, those studies provide the only available data. Also, we believe it is unlikely that a limited improvement in deceleration depth and duration has clinical relevance. The sample size is calculated for each of the subgroups of suboptimal and abnormal FHR tracings. We believe it is important to assess the effect of the intervention in these subgroups because foetuses with lower initial pO_2_ levels may profit more from maternal hyperoxygenation [29].

Regarding the subgroups of AGA and SGA infants, we did not increase our sample size to reach an adequate number of participants in the SGA group. Nevertheless, we find it interesting to investigate whether there is a different effect of maternal hyperoxygenation in SGA infants compared with AGA infants.

Because of organisational challenges, it is not possible to conduct a double-blind trial. Hence patients and delivery room staff are not blinded to the patient’s allocation to a study group, which may lead to observer bias. However, analysis of FHR tracings will be done using a computerised algorithm, to minimise bias, and the investigators judging the CTGs and secondary outcome measures are blinded to the study arm.

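### The 67 patients per CTG group do not follow from the printed inputs, which require 18 per arm (36 per CTG group), so the stated 80% power per group does not match the stated assumptions

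*Protocol article*

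**What the plan says.** All the inputs are in the protocol article, under Sample size calculation.

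- Groups: "The study consists of two study groups: one group with suboptimal FHR patterns and one group with abnormal FHR patterns". A study group is thus a CTG class, not a treatment arm.
- Target: "We aim for the study to have 80% power and a level of significance of 0.05 in both groups".
- Effect: "we expect ≥ 50% improvement in the oxygen group and 0% in the control group", for both CTG classes.
- Spread: "We estimated a mean improvement of 50% with an SD of 50% in each group".
- Test: a G*Power calculation "for a two-tailed Mann-Whitney" U test.
- Result: the calculation "resulted in a sample size of 67 patients in each study group".
- Allowance: "We added an extra 20% to compensate for missing data". Doubling for the two CTG classes then gives a total of 162.

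The Discussion confirms the unit: "The sample size is calculated for each of the subgroups of suboptimal and abnormal FHR tracings". The Methods paragraph of the abstract gives a different total, 116.

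**The concern.** A difference of 50 points with an SD of 50 points is one standard deviation, a very large effect. Detecting it with 80% power takes fewer than 20 patients per arm, so 67 per CTG group looks too large. It is also odd, which a total for two equal arms would not be. The same number is familiar as the per-arm requirement for an effect half that size.

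What is at stake is how to read the result within each CTG class. The Discussion gives a clinical reason for studying the two classes separately and says the trial was sized for each. At about 98% power, a null result in one class would be strong evidence against a 50-point effect. At about 50% power, it would be inconclusive. The article does not let a reader tell which applies.

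**Working it through.** **Inputs (Sample size calculation):** difference 50 − 0 = 50 points; SD 50 points; two-sided α = 0.05; power 80%; Mann-Whitney U.

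**Assumptions added here:** the SD of 50% applies to both treatment arms; allocation is 1:1 (the article gives blocks of four or six but no ratio); the two arms are balanced within each CTG class.

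**1. The plan's total.** 67 × 1.2 = 80.4, rounded up to 81 per CTG group; 81 × 2 = 162. The total follows from 67 only if 67 counts both arms of one CTG class, that is 33 and 34 per arm.

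**2. Effect size.** d = 50 / 50 = 1.0.

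**3. Method.** G*Power-type calculation: multiply each arm size by the asymptotic relative efficiency (ARE) of the Mann-Whitney test against the t test, then use the noncentral t distribution. With n₁′ = ARE × n₁ and n₂′ = ARE × n₂, the noncentrality is d × √[n₁′n₂′ / (n₁′ + n₂′)] on n₁′ + n₂′ − 2 degrees of freedom. ARE is 3/π for a normal parent and 0.864 for the minimum-ARE option.

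**4. Required n per arm for 80% power, two-sided 0.05**

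| Parent option | d = 1.0 | d = 0.71 | d = 0.5 |
|---|---|---|---|
| Normal (3/π) | 18 | 34 | **67** |
| Minimum ARE | 20 | 38 | 74 |
| Logistic | 16 | 30 | 59 |
| Laplace | 12 | 22 | 43 |
| Plain t test | 17 | 33 | 64 |

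For d = 1.0 with a normal parent, 17 per arm gives 78.8% and 18 gives 81.2%, so the requirement is 18 per arm, or 36 per CTG group. Simulated Mann-Whitney power at 18 per arm is 80.7%. Across the options the range is 12 to 20 per arm, or 24 to 40 per CTG group. One-sided tests and α = 0.025 widen it only to 9 to 24 per arm. Nothing at d = 1.0 and 80% power gives 67, per arm or per CTG group.

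**5. Where 67 does appear.** At d = 0.5 with a normal parent, 66 per arm gives 79.5% and 67 gives 80.1%, so 67 is exactly the per-arm answer. A near match as a two-arm total is d = 50 / (50 × √2) = 0.71, which gives 34 per arm, or 68.

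**6. Power of the planned size (normal parent)**

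| Evaluable patients | d = 1.0 | d = 0.71 | d = 0.5 |
|---|---|---|---|
| 67 per CTG group (33/34 per arm) | 97.6% | 79.5% | 50.3% |
| 81 per CTG group (40/41 per arm) | 99.1% | 86.6% | 58.3% |
| 134, both CTG groups combined (67 per arm) | 99.99% | 97.8% | 80.1% |

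Simulation at 33/34 per arm agrees: 97.8% at d = 1.0 and 50.7% at d = 0.5.

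**7. Detectable difference.** At 33/34 per arm, 80% power is reached at d = 0.712. With SD 50% that is 0.712 × 50 = 35.6, about 36 points.

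**8. If the abstract's 116 is the target.** 116 / 2 = 58 per CTG group; 58 / 1.2 ≈ 48 evaluable, or 24 per arm. Power per CTG group is then 91% at d = 1.0 and 38% at d = 0.5. For the combined group (48 per arm) at d = 0.5 it is 66%.

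**The case against.** The strongest reply is that the article states an aim of 80% power, and under the only inputs it prints, 67 per CTG group delivers about 98%. On that reading the aim is exceeded and the defect is only a calculation that cannot be reproduced. This largely stands. It is why the point is a mismatch between inputs and result, not a demonstrated lack of power. It does not remove the mismatch.

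A reader might infer from the exact match at d = 0.5 that each CTG group really has only a coin-flip chance of success. The article does not support that: neither d = 0.5 nor an SD of 100% is printed anywhere, and d = 0.71 comes close to 67 as a two-arm total, with nearly 80% power.

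A reader might also infer that the closing recommendation against oxygen after a null result rests on about 50% power. It does not. That recommendation concerns the trial's results as a whole, the combined group is also analysed, and with 134 evaluable patients it keeps 80% power even at d = 0.5.

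Two further readings fail. The article adds 20% for missing data but never claims to withstand a 20% loss, so multiplying by 1.2 contradicts nothing it states. Its wish to limit exposure is set against a very large trial powered on neonatal outcomes, and 162 patients do not conflict with that.

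Finally, d = 1.0 is itself a reading. Since groups are first defined as CTG classes, an SD stated for each group is not explicitly an SD for each treatment arm. It is the natural reading, but the authors should confirm it.

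**Conclusion.** The point holds as a mismatch between inputs and result. The printed assumptions need 36 patients per CTG group (24 to 40 across the parent options), not 67. The stated 80% per group does not match the stated assumptions, under which power at 67 per group is about 98%.

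That a per-arm figure for d = 0.5 was carried forward as a two-arm total is the exact numerical fit, but it remains an inference. Only in that case would each CTG group have about 50% power.

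The conclusion rests on SD 50% in both treatment arms, 1:1 allocation, balanced arms within each CTG class and a total of 162. The figure of 18 per arm assumes a normal parent, but no other option rescues 67.

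**What to change.** Re-run the calculation and print the effect size entered, the parent distribution, n per arm and n per CTG group. Reconcile 162 with the 116 in the abstract first, because the power statement depends on it. Then restate power for the size actually planned.

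- **If SD 50% is right and 162 stands:** state that about 33 to 34 evaluable patients per arm in each CTG group give about 98% power for a 50-point difference, and 80% power for a difference of about 36 points.
- **If d = 0.5 was intended and 162 stands:** correct the printed SD or effect. State that 80% power applies to the combined group (67 per arm) and about 50% to each CTG group, so that a null result in one CTG group would be inconclusive.
- **If another effect size was entered, or 116 is the target:** print the value used and recompute the power statement in the same way.

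The cost is a rewritten sample size paragraph, with matching edits to the Discussion and abstract. No extra patients are needed. The stated power per CTG group may become less favourable.

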**Methods/design:**

This study is a single-centre randomised controlled trial being performed in a tertiary hospital in The Netherlands. From among cases of a suboptimal or abnormal foetal heart rate pattern during the second stage of term labour, a total of 116 patients will be randomised to the control group, where normal care is provided, or to the intervention group, where before normal care 100% oxygen is supplied to the mother by a non-rebreathing mask until delivery. The primary outcome is change in foetal heart rate pattern. Secondary outcomes are Apgar score, mode of delivery, admission to the neonatal intensive care unit and maternal side effects. In addition, blood gas values and malondialdehyde are determined in umbilical cord blood.

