#### Interim analysis

On account of safety concerns, an interim analysis will be performed when 50% of the patients are included in the study. In this analysis, we will compare the number of neonates with a 5- minute Apgar score < 7 and/or pHa < 7.05, the number of admissions to the NICU and perinatal death in both groups (all neonates that received oxygen in both suboptimal and abnormal CTG groups versus ‘conventional care’ group). If the interim analysis shows a significant difference, we will terminate the study. This interim analysis is performed exclusively for safety reasons; because the primary outcome measure (FHR) will not be analysed during the interim analysis and power analysis is based on the primary outcome, adjustment of the significance level is not required.

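### The abstract randomises 116 patients and the sample-size section requires 162, so the recruitment target and the interim time point are each stated two incompatible ways

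*Protocol article*

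**What the plan says.** The Methods/design paragraph of the abstract states that "a total of 116 patients will be randomised to the control group" or, as the sentence continues, to the intervention group. So 116 is the total over both arms.

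The Sample size calculation section defines two study groups by CTG category, suboptimal and abnormal, and sets the error rates for each: "We aim for the study to have 80% power and a level of significance of 0.05 in both groups". The effect is given as "we expect ≥ 50% improvement in the oxygen group and 0% in the control group", and the spread as "We estimated a mean improvement of 50% with an SD of 50% in each group". The calculation was made "for a two-tailed Mann-Whitney" U test and "resulted in a sample size of 67 patients in each study group". After a 20% addition for missing data, and with two CTG groups, the section concludes that "we need 162 patients to participate". The Discussion repeats that the sample size was calculated for each CTG subgroup.

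The Interim analysis section says that "an interim analysis will be performed when 50% of the patients are included in the study". It gives no number, and a significant safety difference at that look ends the trial.

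**The concern.** Both figures are given as the size of the same trial. Neither is marked as superseded, as an actual accrual figure, or as referring to a different population. The sections on recruitment, interim analysis, discussion and trial status say nothing that would settle the matter.

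Three things depend on the total:

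- **When recruitment stops.** Delivery-room staff and patients know the allocation, so a stopping point that can be read two ways is better closed in advance.
- **When the safety interim takes place.** It is the only interim look described, and the two readings place it 23 patients apart.
- **The power actually achieved in each CTG group.** The article says that the design was sized for each group separately.

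**Working it through.** **1. The plan's own figure.** 67 × 1.2 = 80.4, rounded up to 81 per CTG group; 81 × 2 = 162. The step from 67 to 162 reproduces exactly.

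**2. Can 116 come from the same chain?** 116 / 2 = 58 per CTG group, and 58 / 1.2 = 48.3 before the addition, not 67. Nor is 116 the total before the addition, which would be 67 × 2 = 134. The gap is 162 − 116 = 46, and 46 / 162 = 28%.

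**3. Could 162 be women who consent and 116 those randomised?** Consent does precede randomisation in this trial. But two CTG groups of 67 already need 134 analysable patients, more than 116. This reading fails.

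**4. Interim.** 50% of 116 is 58; 50% of 162 is 81; the difference is 23.

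**5. Power per CTG group at the stated effect.** Inputs from the Sample size calculation section: difference 50 − 0 = 50 points, SD 50, so d = 50/50 = 1.0; two-sided 0.05; Mann-Whitney test. Assumed here: 1:1 arms (the article gives only block sizes of four and six), an even CTG split, and 20% of patients lost.

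Method: asymptotic relative efficiency (ARE). With n evaluable per arm, put m = n × ARE and use the noncentral t distribution with 2m − 2 degrees of freedom and noncentrality d√(m/2). ARE is 3/π for a normal parent distribution and 0.864 at its minimum.

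| Total | Per CTG group | Evaluable per arm (×0.8, /2) | Power, normal parent | Power, minimum ARE |
|---|---|---|---|---|
| 116 | 58 | 23.2 | 0.90 | 0.87 |
| 162 | 81 | 32.4 | 0.97 | 0.96 |

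Undoing the addition by dividing by 1.2 instead gives 24.2 and 33.8 per arm, with power 0.91 and 0.98 (normal parent).

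**6. Does 67 follow from the stated inputs?** At d = 1.0, two-sided 0.05 and 80% power, the same method needs 18 per arm (normal parent) or 20 (minimum ARE), that is, 36 to 40 per CTG group. Changing one setting at a time does not reach 67 either:

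- 90% power: 24 to 26 per arm.
- 95% power: 29 to 32 per arm, at most 64 per CTG group.
- Alpha 0.025: 22 to 24 per arm.

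The figure 67 is exactly the number per arm at d = 0.5 (two-sided 0.05, 80% power, normal parent). The article uses it as the total of a CTG group.

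**7. Sensitivity (assumptions, not figures from the article).**

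- *Uneven CTG split at d = 1.0.* With 36 evaluable patients needed per CTG group, the smaller group must hold at least 36 / (0.8 × 116) = 39% of patients at 116, or 36 / (0.8 × 162) = 28% at 162. If it holds 30%, power there is about 0.70 or 0.84.
- *If d = 0.5 had been the real input.* Power per CTG group with an even split would be about 0.37 at 116 and 0.49 at 162. Two CTG groups would then need 4 × 67 = 268 evaluable patients.

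**The case against.** The strongest reply is that this is a slip in an abstract. The article condenses a full protocol (version 8), which is not shown and may carry a single total. The intended power is not in doubt either, since 80% per CTG group is stated, and both totals exceed it on the article's own inputs.

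Much of this stands. A reader might infer that the power per CTG group is undefined, or that a trial of 116 abandons the promise of adequate power in both CTG groups. The document does not support that. The target power is explicit, and at the only effect stated, with an even split, 116 gives about 90%. Lower values arise only from a smaller effect or an uneven split. The article quantifies neither, although its Discussion allows that the 50% effect may be an overestimate.

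Nor should 116 be treated as the figure without a basis and 162 as the sound one. At 90% power the stated effect gives 24 per arm (normal parent); 24 × 1.2 = 28.8, rounded up to 29, and 29 × 4 = 116. The article states 80%, so this is a possible origin and not a fact, but it means that 116 cannot be dismissed as a misprint. The 67 behind 162, by contrast, cannot be reproduced from the stated inputs.

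Condensation does not remove the conflict. The point is not that detail is absent but that two stated totals are incompatible. What the full protocol says cannot be checked here, so the finding concerns the published article.

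**Conclusion.** The contradiction is real and cannot be resolved from the article: 116 against 162, a gap of 46 patients, with the interim at 58 or 81. The recruitment target and the interim time point each need correcting.

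The effect on power is narrower. Achieved power per CTG group depends on the total, but at d = 1.0 it is about 90% or 97%, above 80% either way. This rests on 1:1 arms, an even CTG split, 20% loss and a normal parent distribution; the least favourable ARE lowers it only to 87% or 96%. An underpowered trial at 116 is not shown.

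A second error bears on the remedy: 67 per CTG group does not follow from a 50-point difference with SD 50. Choosing 162 and amending only the abstract would therefore leave a derivation that does not reproduce.

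**What to change.** - State one total in the abstract and in the Sample size calculation section.
- Whichever total is kept, derive it from inputs that yield it: difference, SD, power, alpha, and whether the base number is per arm or per CTG group. If a standardised effect other than 1.0 was used, say so and correct the stated inputs.
- For that total, give the planned numbers and power per CTG group and per arm. Label any power at a smaller effect or with an uneven CTG split as an assumption.
- Give the interim as a patient count that matches the total: 58 if it is 116, 81 if it is 162.

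The cost is a correction of the text. The stated power may change; no additional patients are required.

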#### Data analysis

IBM SPSS Statistics software (version 24; IBM, Armonk, NY, USA) will be used to perform statistical analysis of the study results. Assuming non-normal distribution, the primary clinical outcome will be analysed with a Mann-Whitney *U* test for differences between the intervention and control groups and a Wilcoxon matched-pairs test for changes within the same participant. When outcome data are found to be normally distributed, independent samples *t* tests (two-tailed) will be used to analyse differences between the intervention and control groups, and paired *t* tests will be used for changes within the same participant. Outcome measures will be calculated for the combined group and the subgroups of suboptimal and abnormal FHR tracings, as well as for small for gestational age (SGA, lower than 10th percentile) and appropriate for gestational age (AGA) neonates. In the intervention group, oxygen may not be applied, owing to practical concerns such as very quick progression of labour. Therefore, we will perform both per-protocol and intention-to-treat analyses. In the per-protocol analysis, parturients who actually received oxygen will be compared with those who did not receive oxygen. In addition, unjust inclusions will be excluded from this analysis.

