To investigate the effect of maternal hyperoxygenation in the presence of foetal distress on the release of free oxygen radicals, MDA is estimated in umbilical cord blood. MDA is the peroxidation product of membrane polyunsaturated fatty acids. We chose to measure this marker for oxidative stress because it was used in prior studies performed during labour and it is related to vaginal birth, non-reassuring FHR tracings, maternal hyperoxygenation and acidaemia in arterial cord blood [36, 37, 39, 41]. We realise that differences in values in umbilical cord blood may be confounded by mode and duration of delivery; therefore, we will correct the results for the mode of delivery. A practical ground on which to choose this marker is that it is the only marker for oxidative stress that can be estimated accurately in Dutch laboratories. In the intervention group, oxygen administration will be continued until delivery to enable analysis of its effect on cord blood gas values and MDA.

Despite some important limitations of this study, we believe this is the best possible way to perform a study while restricting safety issues. If the results do not show any improvement in FHR, we believe that maternal hyperoxygenation should not be used as a treatment for foetal distress. However, if a beneficial effect is demonstrated, we will design a multicentre RCT to investigate the effect on neonatal outcome.

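### The per-protocol analysis is in fact an as-treated comparison: untreated oxygen-arm women are counted with the controls, and neither it nor intention-to-treat is named primary

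*Protocol article*

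**What the plan says.** All references are to the protocol article.

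- **Data analysis** foresees non-receipt: "In the intervention group, oxygen may not be applied, owing to practical concerns such as very quick progression of labour". For that reason, "we will perform both per-protocol and intention-to-treat analyses". Neither is called primary.
- The same section defines the per-protocol contrast as one in which "parturients who actually received oxygen will be compared with those who did not receive oxygen". The only removal stated is that "unjust inclusions will be excluded from this analysis". It does not say that untreated oxygen-arm women are excluded, and it states no adjustment for this contrast.
- **Discussion** accepts, for the oxidative-stress marker, that "differences in values in umbilical cord blood may be confounded by mode and duration of delivery", and continues: "therefore, we will correct the results for the mode of delivery". Duration is named as a confounder but is not in the stated correction.
- **Interim analysis** describes one side of the safety comparison by exposure, "all neonates that received oxygen in both suboptimal and abnormal CTG groups", and the other as the conventional-care group.

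**The concern.** A per-protocol set normally keeps each woman in her randomised arm and leaves out those who did not follow it. Here the grouping is by receipt, so an untreated oxygen-arm woman changes sides.

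Fast labour can prevent receipt in the oxygen arm only. A fast-labouring control is still a control. The oxygen group therefore loses its fast labours, while the comparator keeps its own and gains those from the other arm. If such labours differ in foetal heart rate (FHR) change, cord gases or mode of delivery, the contrast mixes that difference with any effect of oxygen.

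The stake is interpretation. If the two analyses disagree, the text does not say which decides, and the confounded one carries a label that readers take to mean a compliance analysis. The Discussion ties both a practice conclusion and a follow-on multicentre trial to the result.

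**Working it through.** **No planned figure to reproduce.** The document gives no non-receipt rate and no outcome difference for untreated women. What follows is an illustration on assumed inputs.

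**Inputs**
- q, the share of labours too fast for oxygen, equal in both arms by randomisation. Assumed 10–20%.
- D, how much worse the outcome is in those labours, in percentage points of FHR improvement. Assumed 25–50, that is 0.5 to 1 SD.
- SD 50 percentage points (Sample size calculation).
- True oxygen effect zero; n women per arm; every fast labour in the oxygen arm goes untreated. Outcomes are centred so that other labours have mean 0.

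**Bias of the contrast as written**
- Received oxygen: n(1 − q) women, none fast, mean 0.
- Did not receive oxygen: n controls contributing a total of −nqD, plus nq transferred women contributing −nqD. The mean is −2nqD / [n(1 + q)] = −2qD/(1 + q).
- Spurious benefit = 2qD/(1 + q).

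**Bias if untreated oxygen-arm women are dropped instead of moved**
- The control mean is −qD and the treated oxygen-arm mean is 0, so the bias is qD.

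**Bias under intention-to-treat**
- Both arms have mean −qD, so the bias is 0.

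| q | D | As written, 2qD/(1+q) | One-sided exclusion, qD | Intention-to-treat |
|---|---|---|---|---|
| 10% | 25 | 5/1.10 = 4.5 | 2.5 | 0 |
| 10% | 50 | 10/1.10 = 9.1 | 5.0 | 0 |
| 20% | 25 | 10/1.20 = 8.3 | 5.0 | 0 |
| 20% | 50 | 20/1.20 = 16.7 | 10.0 | 0 |

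With D = 0 every entry is 0. With D negative (fast labours do better) the sign reverses.

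**Effect on the test.** A simulation under the same assumptions used 81 per arm (162/2), normal errors with SD 50, a two-sided Mann-Whitney test at 0.05 and 3,000 runs per setting. Rejection rates with no true effect:

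| q | D | As written | One-sided exclusion | Intention-to-treat |
|---|---|---|---|---|
| 10% | 25 | 8.6% | 5.7% | 4.8% |
| 10% | 50 | 16.7% | 8.2% | 5.1% |
| 20% | 25 | 16.2% | 8.1% | 4.8% |
| 20% | 50 | 45.3% | 18.0% | 5.0% |

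The bias in points does not depend on n; the rejection rates do.

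**Symmetric restriction.** If the same time-based rule removes the fast labours from both arms, both remaining means are 0 and so is the bias. This is the ideal case, in which fast labour is the only reason for non-receipt.

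**The case against.** Several counter-arguments have force.

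- *Intention-to-treat is planned too.* This stands. A reader might infer that the trial loses its randomisation; it does not. The primary outcome and its test are also worded as intervention against control group, and those groups are defined by random assignment, so the text leans towards intention-to-treat. It still does not say so.
- *The FHR illustration may not fit the women concerned.* This stands in part. The oxygen-arm window runs from 5 to 15 minutes after oxygen starts. A woman who never starts has no such window as written, and very fast labours in either arm may lack a full tracing. Many could have missing or truncated FHR data, not a poor value. The mechanism fits cord gases and mode of delivery better.
- *The link between fast labour and outcome is inferred.* This stands for FHR. The Discussion names duration as a confounder only for cord-blood values. Fast labour is also one example of a practical concern, not the only reason.
- *Moving women is only part of the bias.* Correct. At q = 20% and D = 50, dropping them still leaves 10.0 of the 16.7 points. The comparator is enriched once and the oxygen group depleted once.
- *The interim does not move anyone.* Correct. A reader might infer that untreated oxygen-arm neonates join the interim comparator. That comparator is the conventional-care group, so no transfer is stated. What remains is that those neonates may appear on neither side.
- *The contrast is described openly beside its label.* True, but this settles neither the label nor which analysis leads.

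**Conclusion.** The point holds in limited form. The set called per-protocol is an as-treated comparison by its own definition, non-receipt can follow from a post-randomisation event plausibly related to outcome, and no primary analysis set is named.

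The size is conditional. For an assumed 10–20% non-receipt and an outcome 25–50 points worse, the spurious difference is 4.5 to 16.7 points. The upper value of D equals the trial's whole hypothesised effect, so the top of the range is a strong assumption. The documents support no single value and no direction, and a reader should not conclude that the planned contrast will favour oxygen. The definitional fault does not depend on these numbers.

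**What to change.** 1. State that the primary analysis is intention-to-treat, with women analysed as randomised.
2. Define the per-protocol set within randomised arms: exclude, and never move, women who did not get their allocated care, along with the wrongly included.
3. Preferably apply one time-based eligibility rule to both arms, counted from the start of the study protocol, because exclusion from the oxygen arm alone still leaves a bias of qD. Such a rule conditions on a post-randomisation event and does not cover other reasons for non-receipt, so the set remains supportive.
4. If the received-versus-not-received comparison is kept, call it as-treated and exploratory.
5. For the interim, state that the safety comparison is also shown by randomised arm, so that untreated oxygen-arm neonates are not omitted.

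The cost is a few sentences of analysis text and a slightly smaller per-protocol set. With 81 per arm and 10–20% fast labours, a symmetric rule would remove about 8 to 16 women per arm (81 × 0.10 = 8.1; 81 × 0.20 = 16.2).
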